### Step 2: Program Outcomes and Objectives-Logic Model of Change

In the previous “ikherstel” intervention, the following overall objectives were formulated. After the needs assessment, these objectives were adjusted to align to patients’ problems and needs as identified under step 1:

To enhance recovery by giving clear and simple instructions for the RNA;To stop inconsistent recommendations from different health care providers;To take away the insecurity with respect to postoperative course, symptoms, and complications.

The following overall objectives were added to the existing objectives after the needs assessment in step 1:

To provide extra attention and mental support in case of patients with a malignant indication,To encourage patients to a quicker and more intense mobilization and earlier RNA, andTo let patients have more interaction with their health care professional via a web portal.

Specified performance objectives for the further development of the “ikherstel” intervention are presented in Multimedia Appendix 1. To create a matrix of *performance objectives*, the main personal and external determinants of behavior change for each performance objective were operationalized. The Attitude-Social Influence-Self-Efficacy model was used in the IM procedure of the earlier “ikherstel” intervention and was used for the further development of this intervention as well [19]. This model was still considered by the planning group as the most suitable model for recovery and behavior change and, thereby, used to form change objectives [44-49]. Skills, barriers, and facilitators were considered relevant factors for RNA [50,51]. In Multimedia Appendix 2, an example of the performance objective “mobilize quickly and more intense after operation” is presented.

### Step 3: Program Design

The same practical methods and suitable strategies as in the IM article of Vonk Noordegraaf et al were used for the further development of tools and materials of the “ikherstel” intervention as the methods and strategies used in this intervention already had been proven effective [19,52]. For example, self-monitoring of behavior (awareness) and getting direct feedback will be used to stimulate patients to mobilize quickly and more intensively. An activity tracker will be used in the “ikherstel” intervention to encourage this. Multimedia Appendix 3 presents more examples of these methods with preconditions and final tool/materials of the eHealth intervention.

### Step 4: Program Production

The knowledge gathered in the first 3 steps was discussed by the planning group at several meetings to add various appropriate tools to the existing “ikherstel” intervention. A designer/developer specialized in eHealth and mHealth interventions was consulted during some of the meetings. In addition, experienced surgeons, gynecologists, and residents in training outside the planning group were consulted to judge the medical content of the tools. The words “ikherstel.nl” in the internet address of the eHealth intervention means “I am recovering.” The mobile app was made available for iOS and Android mobile phones and tablets. The design of the further developed “ikherstel” intervention for patients undergoing major abdominal surgical and gynecological procedures (this includes open or laparoscopic colectomy and open or laparoscopic hysterectomy) is described below. In Table 1, an overview of all tools of the developed eHealth intervention is presented.

#### Adaptation of Existing “ikherstel” Intervention Tools

##### Website

The website aims to prepare patients in the best possible manner for their surgery and to offer guidance during their recovery process until full recovery and resumption of all activities are achieved. The following tools on the website support this.

**Table 1 table1:** Component of the “ikherstel” intervention regarding each target population.

Tool		Content	Target population
**Website**			
	Information by text and animations about the surgical procedure	Enhancing patient preparation including creating expectations	All participants
	Personalized convalescence plan	Enhancing patient preparation including creating expectations	All participants
	Recovery monitor and recovery report	Monitoring recovery and offering assistance when relevant	All participants
	Video	Increasing the information provision by using several ways to provide this	All participants
	Glossary	Increasing the information provision by using several ways to provide this	All participants
	Frequently asked questions	Increasing the information provision by using several ways to provide this	All participants
	Electronic consultation	Increasing access to care and reducing patient uncertainties and fear related to the recovery process and workload	All participants
	Information about malignancies	Reducing anxiety and uncertainty and increasing the amount of information provision	All participants with malignant disease
	Information about chemotherapy and side effects	Reducing anxiety and uncertainty and increasing the amount of information provision	All participants with malignant disease
	Links for supportive care needs	Creating long-term support to reduce anxiety and uncertainty	All participants with malignant disease
**Mobile app**			
	Information by text	Enhancing patient involvement and recovery expectations and reducing anxiety	All participants with a smartphone
	Insight into the convalescence plan	Creating recovery expectations and improving recovery	All participants with a smartphone
	Recovery monitor and recovery report	Reducing uncertainties and fear related to the recovery process and improving monitoring and transition of postoperative care	All participants with a smartphone
	Creating a packing list	Increasing better patient preparation before admission	All participants with a smartphone
	Section to make notes	Increasing better patient preparation before admission and during in-hospital stay	All participants with a smartphone
**Activity tracker**			
	Monitoring and giving feedback on recovery	Reducing uncertainties and fear related to the recovery process, which may improve recovery	All participants with a suitable smartphone for the activity tracker

###### Making a Personalized Convalescence Plan

A personalized and tailored convalescence plan, including advice about resumption of (work) activities is the most important tool on the website. The specific tailored convalescence recommendations were developed for relevant types of abdominal surgical procedures by using a modified Delphi procedure [53,54]. On the website, information will be tailored for each patient, offering the opportunity to enhance patient involvement. This is possible as some data are already prefilled when patients receive their website account (eg, surgical procedure, sex, and hospital). This tool will enhance recovery by giving clear and simple instructions for the RNA and will stop inconsistent recommendations from different health care providers.

###### Providing Information About the Surgical Procedure and Recovery Process

Information per treatment phase (preoperative, perioperative, and postoperative) will be provided by text and images. These services will contribute perioperative to the patients’ awareness and expectations; both factors have proven to be important predictors of the length of recovery. Information will also have a positive effect on anxiety and satisfaction because the patients can prepare themselves better for the surgery. Postoperative information will be offered about the recovery period and common postoperative complaints. This could support patients during this period and may help them with feelings of insecurity. In addition, practical advice about when, how, and whom to contact in case of complaints will be provided. Patients will be helped in deciding whether to contact a health care professional in case of complaints or complications during their recovery. Frequently asked questions will be added as well and these were formulated based on main topics in patients’ brochures and Web-based patient discussion forums. This tool will take away the insecurity with respect to the postoperative course, symptoms, and complications.

###### Getting Feedback on Recovery by a Recovery Monitor and Recovery Report

The recovery monitor and report are tools to identify recovery problems and give patients feedback on their recovery progress. Patients will be asked to indicate in a recovery monitor to what extent they have resumed their activities, which will be subsequently graphically displayed in a recovery report allowing them to track their progress. It also aims to improve monitoring and transition of postoperative care. After the patient has given consent, the Web portal can be accessed by a health care professional in secondary care to monitor patients’ recovery and, thus, identify recovery problems.

##### Developing the Materials and Tools of the Revised “ikherstel” Intervention

###### Providing Information on the Website

For patients who will receive adjuvant chemotherapy, information about this treatment, including side effects, is provided on the website. This will provide extra attention and mental support in case of patients with a malignant indication. Videos are also added on the website. Videos are considered the most appropriate medium to deliver an informative message to patients because of the influence of modeling behavior on attitude [55]. Videos about the admission day, the surgical procedures, receiving and managing a permanent or definitive stoma, the postoperative period, and a simulation of patients and employers to discuss potential RTW problems are provided.

###### Postoperative Consult by Electronic Consultation

In case of recovery problems, patients have the option to ask questions to a health care professional from their own hospital by means of an eConsult via the website. Patients will be informed that eConsults are only suitable for nonurgent questions and that these questions will be answered within 2 working days. In case of urgent questions, they receive a phone number for direct contact. The hypothesis is that patients will be more comfortable and less hampered in resuming their activities with the opportunity to ask questions whenever they prefer. This tool will let patients have more interaction with their health care professional via a Web portal.

##### Mobile Phone App (Mobile Health)

All information which is available on the website is also available on the mobile phone app (“ikherstel” app), which will be synchronized with the website. This includes among others the convalescence plan that patients created on the website. A section to make notes and the option to compose a list of what to pack when being admitted to the hospital will also be available on the app. If patients do not have a smartphone, they will only use the website. This tool will enhance recovery by giving clear and simple instructions for the RNA and will stop inconsistent recommendations from different health care providers (see Multimedia Appendix 4).

##### Activity Tracker

An activity tracker that measures the daily step count can be linked to the “ikherstel” application for patients with a smartphone. This tracker will be used as a support tool for patients to monitor and to give feedback on their recovery. The average daily step count in the week before surgery will be set as their baseline measurement and, thereby, target postoperative activity level. The daily step count will be postoperative graphically displayed in the app as a percentage of their target activity level, including a target level the patient is expected to reach. Patients will be asked to wear the activity tracker in the first 4 weeks after surgery, and again after 8 weeks as the hypothesis is that baseline activity level should be reached in this week. This tool will encourage patients to a quicker and more intense mobilization and earlier RNA.

##### Pretest of Materials

In total, 10 patients and a representative sample of health care professionals evaluated the demo version of the eHealth “ikherstel” intervention. Patients got 3 weeks to test the intervention before they were interviewed by the researcher. Semistructured interviews were conducted with patients who also had participated in the FGDs. Health care professionals were asked to judge the demo version on several items (eg, layout, comprehensibility of all informative text). The test patients were satisfied with the content of the information, the way it was delivered, and the messages (source and style). They also found all text provided on the website as very useful. However, a few remarks for improvement were suggested. These were related to supplying more detailed information about the side effects of chemotherapy, adding more attention to mental support, and less complicated sentences. All test patients would like to use the intervention if they will have surgery again.

#### Refinement and Production of Materials After Testing

After participants’ and health care professionals’ feedback, minimal adjustments were made. Mainly textual changes were made to simplify and order sentences. This resulted in the final eHealth intervention that was used to perform the RCT.

### Step 5: Program Implementation Plan

Patients undergoing major abdominal, general surgical, or gynecological procedures were identified as new program users. No new professionals were identified as program users as the introduction and implementation of the program would remain in the perioperative phase also for the extended patient group. The 7 hospitals that participated in the earlier performed “ikherstel” study wished to continue the use of the “ikherstel” intervention including broadening the usage of “ikherstel” intervention at the general surgery department of their hospital. Many other general hospitals in different regions in the Netherlands signed the letter of intent to participate in this multicenter study. After a kick-off meeting at the research institute, one meeting with surgeons or gynecologists (depending on the department) and one meeting with nurses per hospital was held to discuss the content and logistics of the study and its implementation. Finally, 10 general surgery practices and 8 gynecology practices (all teaching hospitals) were positive about the further development of “ikherstel” intervention and willing to implement the intervention. They will participate in the evaluation of this intervention through implementation of the eHealth intervention as a supplement to the standard perioperative care given at their hospital.

### Step 6: Evaluation

#### Study Design

The evaluation of the eHealth intervention will be performed by a multicenter single-blinded RCT. The effectiveness and cost-effectiveness of this innovative eHealth care program compared with the usual care given in 11 participating hospitals on RNA and RTW will be evaluated. A process evaluation will also be performed using a mixed-methods design [56].

#### Eligibility Criteria

Patients who will undergo a laparoscopic or open colectomy or hysterectomy and are aged between 18 and 75 years will be contacted. Exclusion criteria are surgery without a curative intention, deep infiltrating endometriosis, concomitant surgical procedures, not able to use the internet, unable to understand Dutch questionnaires, malignancy (in case of the hysterectomy), and receiving neoadjuvant treatment.

#### Outcome Measures

Our primary outcome measure is RNA. The Patient-Reported Outcomes Measurement Information System physical functioning item bank version 1.2 will be used to measure limitations in daily activities. A list of 29 most relevant selected activities will be presented to participants before surgery with the goal to select 8 activities, which are most relevant for them in their daily life. They will be asked in the following questionnaires after surgery if they can already perform one of these 8 activities. RNA is defined as the time in calendar days from the day of surgery until a participant has resumed all activities [57,58].

Secondary outcomes are social participation, self-rated health, duration until RTW, physical activity, length of recovery, pain intensity, and patient satisfaction [59-63]. Costs will be measured from a societal and health care perspective and consist of costs of the intervention, health care utilization costs, and costs associated with lost productivity [64,65]. Sociodemographic data and questions regarding expectations about the length of recovery and the amount of anxiety will be assessed at the baseline measurement. Complications will be assessed by reviewing the surgical reports and postoperative notes and scored by using the Clavien-Dindo classification [66]. The outcome measures will be obtained by using questionnaires administered at baseline (approximately 1-2 week preoperative) and at 2, 4, and 6 weeks and 3, 6, 9, and 12 months after surgery. For a total overview of all outcomes per measurement moment of this study, see Multimedia Appendix 5.

#### Sample Size Calculation

To detect a hazard ratio of 1.4 for RNA (corresponding to a decrease in median time to RNA from 10 weeks to 7.14 weeks as a result of the intervention) with 80% power while testing using a 2-sided log-rank test at a significance level of 5%, a total of 318 events need to be observed. The total sample size is set at 354 (177 per arm) to account for an anticipated proportion of 2.5% of patients not returning to daily activities within the 12 month follow-up period and a dropout rate of 10%.

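### The stated 80% power does not match 318 events (80% needs 278 to 283; 318 give about 84% to 85%), and 354 patients, taken as an inflation of 318 events, shows the 10% dropout but not the 2.5% non-returners.

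*Protocol article*

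**What the plan says.** The Sample Size Calculation (Step 6: Evaluation) gives the whole derivation in two sentences.

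- Effect: "To detect a hazard ratio of 1.4 for RNA", where RNA is resumption of normal activities, "corresponding to a decrease in median time to RNA from 10 weeks to 7.14 weeks".
- Test and target: "with 80% power while testing using a 2-sided log-rank test at a significance level of 5%, a total of 318 events" is given as the requirement.
- Size: "The total sample size is set at 354 (177 per arm) to account for an anticipated proportion of 2.5% of patients not returning"; the horizon for that 2.5% is 12 months, and 10% dropout is named as the second allowance.

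The section on recruitment and allocation gives 1:1 randomization. The article states nothing else that would raise the event count, such as an interim look, a clustering allowance or a different significance level.

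**The concern.** Hazard ratio, power, significance level, sidedness, test and allocation together determine the number of events. The article gives all six, so its event count should follow from them, and it does not. The next step, from events to patients, should then show two allowances, but the arithmetic shows only one.

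This paragraph is the article's only justification for the trial's size on its primary outcome. A reader who uses it to judge how much information the trial was designed to collect would take 80% as the power at 318 events, or 318 as the number of events that 80% power requires. Both are wrong.

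**Working it through.** **Inputs.** Hazard ratio 1.4, 80% power, two-sided 5% log-rank test, 318 events, 354 patients, 2.5% without the event at 12 months and 10% dropout, all from the Sample Size Calculation. Allocation 1:1, from the section on recruitment and allocation. The medians agree with the hazard ratio: 10/7.14 = 1.40. A misprinted effect size is therefore not the explanation.

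**Step 1. Events at the stated 80% power.** z(0.975) = 1.960 and z(0.80) = 0.842, so (1.960 + 0.842)² = 7.849.

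- Schoenfeld: 4 × 7.849 / (ln 1.4)² = 31.396 / 0.1132 = 277.3, so 278.
- Freedman: 7.849 × (2.4/0.4)² = 7.849 × 36 = 282.6, so 283.

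The stated 318 is 12% (against 283) to 14% (against 278) higher. The two standard formulas differ from each other by only 5 events.

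**Step 2. What does reproduce 318?** Required events by Schoenfeld / Freedman:

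| | 80% | 85% | 90% |
|---|---|---|---|
| Two-sided 5% | 278 / 283 | 318 / 324 | 372 / 379 |
| One-sided 5% | 219 / 223 | 255 / 259 | 303 / 309 |

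The only match is Schoenfeld at 85% power, two-sided: 317.2, rounded up to 318.

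**Step 3. Power with 318 events.**

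- Schoenfeld: Φ(√318 × ln 1.4 / 2 − 1.960) = Φ(3.000 − 1.960) = 85.1%.
- Freedman: Φ(√318 / 6 − 1.960) = Φ(2.972 − 1.960) = 84.4%.

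**Step 4. From events to 354 patients.**

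- Dropout only: 318 / 0.90 = 353.3, or 354 as an even total. This reproduces the plan.
- Both losses in sequence: 318 / (0.90 × 0.975) = 362.4, so 363 (364 for equal arms).
- Both losses added: 318 / 0.875 = 363.4, so 364.
- Starting from the events that 80% power needs: 278 / 0.8775 = 316.8 and 278 / 0.875 = 317.7; 283 / 0.8775 = 322.5 and 283 / 0.875 = 323.4. That is about 317 to 324 patients.

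**Step 5. A second route to the same two figures.** 278 / 0.875 = 317.7 gives 318 *patients* at 80% power with both losses included. If that number was labelled as events and divided by 0.90 again, it also gives 354.

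**Step 6. What 354 patients deliver.** If every dropout leaves before the event, 354 × 0.90 × 0.975 = 310.6 events (354 × 0.875 = 309.8 if the losses are added). Power is then 84.2% to 84.3% (Schoenfeld) or 83.5% to 83.6% (Freedman).

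The article gives no timing for dropout, so the next figures are illustrations. They assume exponential times at the stated medians, with 2.5% in each arm not returning within 12 months and dropout unrelated to recovery:

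| Timing of the 10% dropout | Expected events |
|---|---|
| All before any event | about 310 |
| Evenly over the first 4 weeks | about 316 |
| Evenly over the first 6 weeks | about 318 |
| Evenly over the first 8 weeks | about 320 |
| Constant rate over 12 months | about 337 (87% power, Schoenfeld) |

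**The case against.** The strongest reply is that the discrepancy does no harm. The planned size exceeds what 80% power requires, and even with the least favourable timing of dropout the power is about 84%. No event-driven stop is described, so the figure of 318 triggers nothing in the conduct of the trial. This stands, and it limits the weight of the point. It does not remove the contradiction, because 80% power and 318 events cannot both be right for the stated inputs.

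The missing 2.5% is also a small matter: 354 against 363 to 364 is 9 to 10 patients, or 2.5% to 2.8%. That stands too. The mismatch between power and events is the main point and does not depend on it.

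A reader might infer that 318 events cannot be reached with 354 patients. The article does not support that. The count of about 310 requires every dropout to leave before resuming activities, and the article says nothing on timing. With medians of 7 to 10 weeks and follow-up of 12 months, many dropouts could have had the event first; if dropout is spread over six weeks or more, the illustration reaches 318.

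A reader might also infer that 85% power was used and misreported as 80%. The numerical match is exact, but the route in Step 5 gives the same 318 and 354, and on that route the 2.5% was included and dropout was counted twice. The document cannot tell the two apart.

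**Conclusion.** The point holds as an internal contradiction in the stated figures. For the inputs given, 80% power requires 278 to 283 events; 318 events give 84.4% to 85.1%. If 318 is a number of events, 354 shows the dropout allowance but not the 2.5% that the sentence says it includes.

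The result rests on the standard log-rank formulas, 1:1 allocation and inflation by division by the retained fraction. It does not depend on the choice between Schoenfeld and Freedman, which moves the event count by 5 against a gap of 35 to 40.

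The error is conservative. It would be wrong to conclude that the trial is underpowered: 354 patients give about 84% power in the least favourable case and more if dropout comes later. The stated power and event figures need correcting; the design does not need to change.

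**What to change.** Reconcile power, event count and sample size in the Sample Size Calculation. One wording that keeps 354 patients: for a hazard ratio of 1.4 and a two-sided 5% log-rank test, 80% power requires 278 to 283 events; 354 patients are expected to give at least about 310 events if all dropouts leave before the event (about 84% power), and more if dropout is later.

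If 85% was the intended power, state that instead. In either case, say how the 2.5% and the 10% enter the 354, and whether 318 was meant as events or as patients. Only the investigators can settle this from their original calculation.

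Cost: a change of wording. No extra patients and no change to the conduct or analysis of the trial.
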